### **6.8.3 Dosage and administration of test drugs**

Subjects are to receive either one or two intradermal injections at four week intervals for 3 vaccinations and a Booster vaccination at approximately 6 months from Baseline (see Section 6.3). Vaccinations will occur at: Baseline, Week 4, 8 and a booster will be administered at Week 24. Subjects in Group 1 will receive the intradermal injections into each forearm. Subjects in Group 2 will receive the intradermal injections to the one forearm.

Further details on the administration of study vaccine will be provided in the Study Reference Manual.

Prior to each injection, the forearm(s) that are to be injected will be examined and findings from this examination will be documented. The proposed injection site will be 5-10 cm below the elbow joint. The skin should be free from blemishes, scars, heavy hair, veins, moles, skin conditions, sores or tattoos etc. that have the potential to interfere with the detection of local injection site reactions.

Subjects in Group 2 will receive 2 injections to the same forearm, the second injection will be administered approximately 5 cm away radially, not transversely, from the first injection.

Where there is an ongoing injection site reaction an alternative site should be utilised at subsequent vaccination time points. The subsequent vaccination should be located at least 5 cm away from the previous injection site.

Intradermal injections will be carried out by an individual experienced with ID injections as per Appendix 1.

The subject will be instructed to extend their forearm(s) for 10-15 minutes after receiving their vaccination or until the bleb subsides. The injection site will be left open. No cotton wool, adhesive bandages etc. are to be applied over the injection site. The subject will be instructed to avoid touching the injected area(s).

The Investigator or nominee will make the following observations and document findings in the source notes:

- The size of the 'bleb' immediately after injecting in millimetres,
- The size of the 'bleb' during the period that the subject must keep the forearm extended,
- Whether there is an absence of a 'bleb,'
- If the injected material leaked from the skin before 15 minutes,
- If there are any unusual appearances at the injection site.

The subject will be observed for one hour following each vaccination.

#### 6.8.4 Dispensing and accountability

COR-1 is supplied for use only in this clinical study and should not be used for any other purpose. The Investigator's nominee will prepare the vaccine under the Pharmacy Manual set out in a separate document.

Subjects will require the following numbers of vials according to their treatment allocation:

**Table 6. Subject group dispensing requirements**

| Group | Sub-Group | Treatment dose    | Number of COR-1 vials to dispense | Number of placebo vials to dispense |
|-------|-----------|-------------------|-----------------------------------|-------------------------------------|
| 1     | A         | 2 x 500 mcg COR-1 | 1                                 | 0                                   |
|       | B         | 2 x Placebo       | 0                                 | 1                                   |
| 2     | C         | 2 x 500 mcg COR-1 | 1                                 | 0                                   |
|       | D         | 2 x Placebo       | 0                                 | 1                                   |

Should the pharmacist have difficulties drawing up 2 doses of the investigational product/placebo from the one vial, 2 vials may be dispensed.

The Investigator will be responsible for maintaining accurate records for all study medications dispensed and returned. The inventory must be available for inspection by the study monitor. Study product supplies, including partially used or empty vials and the dispensing logs, must be accounted for by the study monitor and returned to the drug repository and at the end of study returned to the Sponsor.

If requested in writing by the Sponsor, unused study medication supplies may be destroyed by the Investigator provided such disposition can be performed safely. Records shall be maintained by the Investigator or any such alternate disposition of the study medication. These records must show the identification and quantity of each unit disposed of, the method of destruction (taking into account the requirements of local law), and the person who disposed of the test substance. Such records shall be submitted to the Sponsor.

## **7 CONCURRENT MEDICATIONS AND TREATMENTS**

At each study visit or contact, the Investigator should question the subject about any medication taken including vitamin supplements and herbal remedies. Any concurrent medications will be recorded in the subject's records and the CRF. Any changes in doses or introduction of a new medication during the course of the study will also be recorded.

### **7.1 Special Dietary Requirements**

There are no special dietary requirements.

### **7.2 Concurrent Medications/Treatments Not Permitted**

#### **7.2.1 Prior to study entry**

Refer to Exclusion Criteria in Section 5.3

#### **7.2.2 During the study dosing period**

Throughout the study medication dosing period, subjects may not receive any of the following concomitant medications:

- Immunomodulating agents (including immunosuppressive agents, interferon or other immune or cytokine-based therapies), and/or systemic chemotherapeutic;
- Chronic treatment with immune-suppressive therapy (stable use asthma inhalers and topical corticosteroids are permitted);
- Anti-viral medications, (both orally and topically) must not be taken during the swabbing assessment periods of the study. The subject should abstain from taking antiviral medications at all other times during their participation in the study unless in the judgement of the Investigator it is in the subject's best interest and Sponsor approval has been obtained prior;
- Topical application of any lotions or the like to the genital region which may interfere with swab collection during the swabbing assessment periods;
- Subjects also should not receive any other vaccines during their participation in this study.

## 8 ADVERSE EVENTS AND TOXICITY MANAGEMENT

### 8.1 Safety Parameters

Safety parameters will include adverse events, vital signs, and clinical laboratory tests.

### 8.2 Adverse Events

An adverse event or adverse experience (AE) is any untoward medical occurrence in a subject or clinical investigation subject administered an investigational product (whether it is the experimental product or the control) and which does not necessarily have a causal relationship with the investigational product. An AE can therefore be any unfavourable and unintended sign, symptom, or disease temporally associated with the use of a medicinal product, whether or not considered related to the medicinal product. Pre-existing events, which increase in frequency or severity or change in nature during or as a consequence of use of a drug in human clinical trials, will also be considered as adverse experiences. AEs may also include pre- or post-treatment complications that occur as a result of protocol-mandated procedures (e.g. invasive procedures such as biopsies).

Any AE (i.e. a new event or an exacerbation of a pre-existing condition) with an onset date after obtaining written informed consent up to the last day on study (including the follow-up, off study medication period of the study), should be recorded as an AE on the appropriate CRF page(s).

An AE **does not** include:

- Medical or surgical procedures (e.g. surgery, endoscopy, tooth extraction, transfusion); the condition that leads to the procedure is an adverse event;
- Pre-existing diseases or conditions present or detected prior to start of study product administration, that do not worsen;
- Situations where an untoward medical occurrence has not occurred (e.g. hospitalisation for elective surgery, social and/or convenience admissions);
- Overdose of either study product or concomitant medication without any signs or symptoms unless the subject is hospitalised for observation.

The subject will be instructed on the completion of the Diary Booklets that will serve as supporting documentation for solicited signs or symptoms after each vaccination including local injection site reactions and systemic symptoms and also genital HSV-2 symptoms (during swabbing assessments). Entries in the diary booklets shall be evaluated and graded for severity and causality by the Investigator (see Section 8 and Appendix 2). Clinically significant signs and symptoms reported in the diary card will be entered in the CRF.

Injection site reactions may include:

- Pain/tenderness;
- Erythema;
- Swelling/Induration; or
- Other.

Systemic symptoms may include:

- |                    |                     |
|--------------------|---------------------|
| • Hypersensitivity | • Rigors;           |
| • Headache;        | • Arthralgia        |
| • Fatigue;         | • Nausea/Vomiting;  |
| • Myalgia;         | • Diarrhoea;        |
| • Malaise;         | • Light headedness; |
| • Fever;           | • Dizziness.        |

Additionally the subjects will be provided with HSV-2 Outbreak forms should they have a genital herpes recurrence outside the shedding assessment periods

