A total of 143 local ADRs were reported during the study period by 21 subjects (95.5%). The number of local ADRs reported increased with increasing dose of COR-1. Erythema and induration were the most frequently reported injection site reactions, occurring in at least one subject in each treatment group at some point during the vaccination phase. Erythema was reported more frequently in the 100 mcg, 300 mcg and 1 mg COR-1 treatment groups. Induration was reported more frequently in the 1 mg COR-1 treatment group. All injection site reactions were classified as mild in intensity.

A total of 14 systemic ADRs were reported during the study period by four subjects (18.2%). The most frequently reported were headache, fatigue, chills, malaise, pain and pyrexia. There were no trends in the frequency of systemic ADRs by treatment group. All the systemic ADRs reported were classified as mild in severity.

Review of haematology and biochemistry results revealed no trends or notable changes over time following vaccination with COR-1 at any dose level. There were no trends or notable findings in vital signs following each vaccination with COR-1 at any dose level.

A review of the safety data suggests that 3 ID vaccinations of the COR-1 vaccine at three weekly intervals were safe and well tolerated.

No anti-HSV gD2 antibodies were detected in any subject by ELISA, indicating that no subjects had seroconverted to COR-1 during the study based on the utilised method.

IFN- $\gamma$  production by T cells specific for gD2 antigen was induced in 19 of the 20 subjects who completed the study as planned and was considered a cell-mediated response to the COR-1 vaccine. The response rates were similar in all treatment groups with 100.0% of subjects responding to the COR-1 vaccine in the 10 mcg, 30 mcg, 300 mcg and 1 mg groups and 75.0% responding in the 100 mcg group.

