### 4.2 Endpoints

#### Primary endpoints:

The primary endpoints of this study are:

- Incidence and severity of adverse events in each treatment group, including vaccine related adverse events:
  - Incidence and severity of local reactions (soreness, redness, induration, ecchymosis, oedema, itching and paraesthesia) at the site of vaccination;
  - Incidence and severity of systemic reactions (fatigue, myalgia, malaise, fever, rigors, arthralgia, nausea, diarrhoea, light headedness, dizziness, hypersensitivity and headache).

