#### **6.3.2.4 Visit 10 / Week 8 + 48 hours**

Visit 10 is to be scheduled for all subjects 48 hours after receiving their third vaccination at Visit 8. There is a +/- 12 hour window for this visit.

All subjects will have their injection sites assessed by the Investigator or designee. Any reactions will be recorded in the source notes and the corresponding CRF page. All subjects regardless of whether they have had an injection site reaction will have a photograph taken in a standardised manner. Please refer to Section 6.4.8.

A symptom directed physical examination will be performed (see Section 6.4.2).

Skin biopsies will be taken from all subjects who provide consent at their injection sites. Please refer to Section 6.4.11.

Adverse event, occurrences of HSV-2 outbreaks and concurrent medication questioning will occur (see Section 7 and 8).

The Injection Site Reaction Diary will be reviewed and returned to the subject.

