### 6.4.2 Physical examination

A complete physical examination (including head, ears, nose, throat, lungs, lymph nodes, heart, abdomen, skin and genital region) will be conducted to determine study eligibility at screening. A symptom directed physical examination will be performed at subsequent visits as defined in Section 6.3. The symptom directed physical examinations will be performed based on signs and symptom the subject has reported verbally and/or documented in the diary booklets. A symptom directed physical examination may also be performed if in the opinion of the Investigator it is required.

Prior to each injection, the forearm that is to be injected will be examined and findings from this examination will be documented.

At each visit, following Visit 5, the subject's injection sites will be inspected and any reactions will be graded. Please refer to Section 8. Any reactions should also be captured as adverse events within the CRF.

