##### Injection Site Reaction Diary:

---

The aim of this Diary is to collect information about injection site reactions for 7 days following each vaccination. Information that is to be collected includes the presence of:

- Pain/tenderness;
- Swelling/induration;
- Erythema; or
- Other findings.

Subjects will be provided with a ruler to enable the subject to measure and record the size of any injection site reactions that occur in millimetres (mm). Subjects will be instructed to measure the longest diameter of the reaction area. Instructions on the measurement of reactions will be provided to the subjects within their Diary booklet. Injection site reactions will be graded in accordance with the FDA Guidance for Industry document entitled *Toxicity Grading Scale for Healthy Adult and Adolescent Volunteers Enrolled in Preventive Vaccine Clinical Trial* (2007) except for pain and tenderness (see Section 9.2.1).

The Injection Site Reaction Diaries will be issued and collected at the following visits:

- Vaccination 1- Issued at Visit 5, collected at Visit 6;
- Vaccination 2- Issued at Visit 7 and collected at Visit 8;
- Vaccination 3 – Issued at Visit 9, reviewed at Visit 10, and collected at Visit 11; and
- Booster Vaccination/Placebo – Issued at Visit 16 and collected at Visit 17.

When each Diary is returned by the subject, the site staff will check that it is complete and legible while the subject is in the clinic.

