### 8.2.1 Assessment of AEs

All AEs will be assessed by the Investigator and recorded on the appropriate CRF page, including the date of onset and resolution, severity, relationship to investigational vaccine/placebo, outcome and action taken with study medication. See Appendix 2 for details of toxicity grade scales (TGS) relevant to vital signs, local reactions to injectable product, systemic signs and symptoms, systemic illness, and clinical laboratory adverse events.

In addition, injection site reactions will be graded by an Investigator or designee, according to severity. It is anticipated that the subjects may find it difficult to differentiate pain and tenderness (Norquist et. al. 2012). For this reason pain and tenderness have been combined with the following grading scale:

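### Conflicting rules on which post-vaccination reactions are solicited and entered in the CRF may lead to undercounting of the primary safety endpoint

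*Protocol*

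**What the plan says.** **Endpoint.** Protocol section 4.2 (repeated in the synopsis) makes two lists part of the primary endpoint: "Incidence and severity of local reactions (soreness, redness, induration, ecchymosis, oedema, itching and paraesthesia) at the site of vaccination" and "Incidence and severity of systemic reactions (fatigue, myalgia, malaise, fever, rigors, arthralgia, nausea, diarrhoea, light headedness, dizziness, hypersensitivity and headache". Neither carries a severity or significance threshold.

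**Diary to CRF.** Section 8.2 has the investigator grade diary entries for severity and causality, then states: "Clinically significant signs and symptoms reported in the diary card will be entered in the CRF". The qualifier is not defined and is not tied to a grade.

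**Other routes to the CRF.** For injection sites inspected at each visit after Visit 5, section 6.4.2 says: "Any reactions should also be captured as adverse events within the CRF". For Visit 10, section 6.3.2.4 says: "Any reactions will be recorded in the source notes and the corresponding CRF page". Section 8.2.1 says: "All AEs will be assessed by the Investigator and recorded on the appropriate CRF page". Section 8.2.2 requires reporting of all AEs whatever their severity, and section 8.2 itself says that any AE after consent should be recorded on the CRF.

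**Diary content.** Section 8.2 describes the diary booklets as supporting documentation for solicited local and systemic symptoms after each vaccination, and lists the systemic ones. Section 6.4.10 is narrower: "The aim of this Diary is to collect information about injection site reactions for 7 days following each vaccination". Its items are pain/tenderness, swelling/induration, erythema and other findings. Footnote 7 to Table 1 also limits the post-vaccination diary to injection site reactions.

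**The concern.** The endpoint counts every listed reaction, but the one sentence that deals specifically with moving diary entries to the CRF names only those judged clinically significant. A site could reasonably read it as the working rule. A Grade 1 reaction is the entry most likely to be left out, and different investigators would draw the line in different places.

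The diary has a parallel problem. A symptom described as solicited in one section but absent from the diary specification in another will be reported only if the subject volunteers it or recalls it when questioned.

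At stake is the completeness of the trial's only primary endpoint. If mild events were lost, incidence would read low and the severity distribution of what remained would shift upward. An analysis plan cannot repair this, because it cannot recover reactions that were never solicited or never entered.

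**Working it through.** There is no plan figure to reproduce. The check sets the passages side by side and then asks what the Phase I data imply.

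**1. Which reactions go to the CRF?**

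| Protocol section | Applies to | Filter |
|---|---|---|
| 4.2 (endpoint) | Listed local and systemic reactions | None |
| 6.4.2 | Sites inspected at each visit after Visit 5 | None |
| 6.3.2.4 | Sites inspected at Visit 10 | None |
| 8.2, AE rule | Any AE after consent | None |
| 8.2.1 and 8.2.2 | All AEs | None |
| 8.2, diary sentence | Signs and symptoms in the diary | Clinically significant |

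The last row does not fit the others.

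**2. Do the unfiltered routes cover the same events?** Only in part. Section 6.4.11 says the injection-site reaction appears after 24 hours and is maximal at 48 hours.

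| Vaccination | Next scheduled clinic visit |
|---|---|
| Dose 1 | Visit 6, one week |
| Dose 2 | Visit 8, one week |
| Dose 3 | Visit 10, 48 hours |
| Booster | Visit 17, one week |

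For three of the four vaccinations no clinic visit is scheduled near the expected peak. The diary is then the only planned day-by-day record of a reaction that has gone by the one-week visit, and that record is what the filtered sentence governs.

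**3. Are the endpoint's terms in the specified diary?**

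- Local, 7 terms: soreness, redness, induration and oedema correspond to listed items. Ecchymosis, itching and paraesthesia do not, so 7 − 4 = 3 fall to other findings.
- Systemic, 12 terms: none is listed in section 6.4.10 or footnote 7. All 12 appear in the section 8.2 list.

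**4. What did Phase I show (section 3.2.4)?**

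- Local: 21/22 = 95.5% of subjects, 143 reactions. "All injection site reactions were classified as mild in intensity".
- Systemic: 4/22 = 18.2% of subjects, 14 reactions, also all mild.
- Together: 143 + 14 = 157 reactions, none above mild.

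**5. Illustration.** Assume the Phase I subject incidence p applies to the 15 + 15 = 30 COR-1 subjects, and let f be the share of affected subjects with at least one reaction entered in the CRF. The expected number of subjects counted is 30 × p × f.

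| f | Local, 30 × (21/22) × f | Systemic, 30 × (4/22) × f |
|---|---|---|
| 1 | 28.6 | 5.5 |
| 0.5 | 14.3 | 2.7 |
| 0 | 0 | 0 |

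The documents give no value for f. If sections 6.4.2, 8.2.1 and 8.2.2 govern, f = 1 and the qualifier removes nothing. The table gives bounds, not an estimate.

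**The case against.** The strongest reply is that the protocol, read as a whole, already requires complete capture. The 8.2 sentence says clinically significant entries will be entered; it does not say the rest are left out. The same section defines an AE broadly enough to include any mild symptom and sends any AE to the CRF. That stands. A reader might infer that only clinically significant reactions can reach the database, and the documents do not support this.

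On systemic symptoms, the diary form is not shown, and section 8.2 says these symptoms are solicited. The item list in 6.4.10 includes other findings and need not be exhaustive. That section also says, under the HSV-2 Symptom Diary, that the booklets have space for adverse events. Subjects receive an Observation Form for events between visits (section 6.3.1.2), and AE questioning takes place one week after every dose and 48 hours after dose 3. So these events have routes to the record. Those routes take unsolicited reports, however, which is not what 8.2 says is collected.

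Two further inferences should be resisted. One is that the comparison with placebo would be uninterpretable. Section 6.6 blinds the assessors to COR-1 versus placebo, so any filter would be applied without knowledge of treatment, and section 11 makes the analysis descriptive. The other is that rates could not be compared with Phase I. That depends on Phase I capture rules, which the protocol does not give.

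The reply leaves two conflicts in place: the 8.2 diary sentence against the other CRF rules, and the 8.2 account of the diary against 6.4.10 and footnote 7.

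**Conclusion.** The point holds as an internal inconsistency that bears on the primary endpoint. Reactions may be undercounted; the documents do not show that they will be. The exposure is confined to mild local reactions that resolve before the one-week visit after doses 1, 2 and the booster, and to systemic symptoms that are not prompted. It arises only if sites follow the 8.2 diary sentence and the diary is as 6.4.10 specifies.

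The size cannot be derived. A reader might infer from Phase I that local incidence could read anywhere from 0% to 95.5%. That is a bound which assumes at its lower end that every mild reaction is discarded and every other CRF rule ignored. What Phase I does support is relevance: all 157 recorded local and systemic reactions were mild, so a filter on significance would act on the type of event this vaccine is expected to produce. This should be fixed, preferably before dosing, because unprompted symptoms cannot be reliably recovered later.

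**What to change.** 1. In section 8.2, delete the words Clinically significant from the diary sentence, and state that every local or systemic reaction recorded in the diary, of any grade, is entered in the CRF per dose with its maximum grade. This brings the sentence into line with sections 4.2, 6.3.2.4, 6.4.2, 8.2.1 and 8.2.2.
2. Align section 6.4.10 and Table 1 footnote 7 with section 8.2 by listing the 12 systemic terms, and ecchymosis, itching and paraesthesia, as items in the 7-day post-vaccination diary. If the diary form already carries them, correct only the text of 6.4.10 and footnote 7.

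The cost is one sentence in 8.2, an edit to 6.4.10 and the footnote, one diary page, a CRF form for solicited reactions if none exists, and slightly more data entry. Visits, sample size and the analysis are unaffected.
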